### Statistical analysis plan

2.9

Linear mixed effect models will be used to assess the effect of the internet-based treatment on vulvar pain, pain acceptance, depression, anxiety, sexual function, and quality of life over time, by applying the intention-to-treat approach. Variables that vary significantly between groups at baseline will further be adjusted for in the model. Linear mixed modelling is a frequently recommended method for its abilities to handle missing data and correlated observations in repeated-measures data (Gueorguieva and Krystal, 2004; Yoo, 2010). The best-fitted model to the data consists of an unstructured covariance matrix using the restricted maximum likelihood (REML) estimation procedure. Baseline, posttreatment and follow-up measures will be used as repeated measures and intervention/control group will be used as fixed factors.

As significant drop-out is common in internet-based interventions, further analyses will be performed. Continuous data will be analysed with general linear models using besides intention-to-treat also per protocol approaches to assess the effects of the intervention on vulvar pain, depression, anxiety, sexual function, and quality of life at different time points (post-treatment and follow-up). Last observation carried forward (LOCF) will be used for the intention-to-treat analysis. Complementary analysis using worst case imputation and analysis using a per-protocol approach without imputation will also be carried out. Effect size will be calculated with Cohen's d. *P* values less than 0.05 will be considered statistically significant. Ordinal (impact of pain on sexual function) and binary data (willingness to perform tampon test and attempt at vaginal intercourse) will be analysed with Mann Whitney's test, Fischer's exact test and multivariate logistic regression, respectively, to assess differences between groups at posttreatment and follow-up. The binary data are referring to secondary outcomes and will be analysed using a per protocol approach only. Descriptive statistics at baseline and the corresponding changes during follow-up both will be provided in tables and graphically. All analyses will be completed using the IBM SPSS statistical package.

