### Study population and recruitment

2.3

Women have been assessed for eligibility since 2016 and the aim is to complete recruitment during 2020. Patients with vulvodynia are recruited from waiting lists for clinical treatment at gynaecological clinics in four counties in Sweden (Falun, Gävle, Uppsala, and Örebro), and through advertisements in social media. The women then receive detailed information about the study over the telephone by the research team. The same information in written form is sent by regular post. Participants are included only after a telephone screening interview performed by one of the researchers, and after they return a signed consent form. A structured questionnaire for diagnostics and evaluation of symptoms developed by the Swedish Working and Reference group for Vulva Diseases, (SFOG, 2013), and structured questions about psychological symptoms, are used for suitability screening in the study. The screening interview is usually scheduled after, but may also occur before, a gynaecologist's appointment. Participants recruited via social media are included in the study only if they can confirm a previous medical diagnosis of vulvodynia and had no ongoing treatment for vulvodynia when they enrol the study. After inclusion, patients fill out the baseline questionnaire and are then randomised to the intervention or control groups.

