### Sample size calculation

2.7

Sample size calculation was based previous clinical experience based on self-reported vulvar pain using a Visual analogue scale, which is a Likert scale between 0 and 10, where 0 represents no pain and 10 represents the worst possible pain; this is regularly assessed with questions on pain at intercourse or tampon insertion, which are posed during the first appointment with gynaecologists at Uppsala University Hospital. A minimum of 26 patients in each group at each time point is estimated to give 80% power for ascertain a difference between the groups at a significance level of *p* < 0.05 for a minimum clinically significant improvement of at least 1.2 units in the Visual analogue scale for vulvar pain, as described above, with an estimated 20% drop-out rate.

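### Covariates for the mixed model are chosen by significance tests of baseline imbalance; the adjustment, including how baseline pain is used, should be fixed in advance

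*Protocol article*

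**What the plan says.** All references are to the protocol article.

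- **Covariate rule (section 2.9).** For the linear mixed model: "Variables that vary significantly between groups at baseline will further be adjusted for in the model". No covariate is named in advance.
- **Role of baseline in that model (section 2.9).** "Baseline, posttreatment and follow-up measures will be used as repeated measures and intervention/control group will be used as fixed factors". The covariance is specified as an "unstructured covariance matrix using the restricted maximum likelihood (REML) estimation procedure". Baseline pain is therefore an outcome row for every participant.
- **Time-point analyses (section 2.9).** "Continuous data will be analysed with general linear models using besides intention-to-treat also per protocol approaches", at post-treatment and follow-up. The article names no baseline term for these models.
- **Significance level (section 2.9).** P "values less than 0.05 will be considered statistically significant"; sidedness is not given.
- **Allocation (section 2.4).** Simple randomisation, with no stratification described.
- **Sample size (section 2.7).** "A minimum of 26 patients in each group at each time point is estimated to give 80% power" for a "minimum clinically significant improvement of at least 1.2 units in the Visual analogue scale for vulvar pain", with 20% drop-out. No SD is given.

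**The concern.** When allocation is random, a significant baseline difference is a chance finding, and its p-value says nothing about whether the variable predicts later pain. Three consequences follow.

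1. The adjustment set is fixed only after the data are seen, and chance decides it. Sections 2.8.1 and 2.8.2 list many baseline scales as well as sociodemographic items, so there are many candidates.
2. A variable with no bearing on pain can enter, while a prognostic one stays out because its imbalance fell short of significance.
3. If baseline pain is the flagged variable, the mixed model contains it as the T0 outcome and as a covariate. The T0 row is then regressed on itself, which is incoherent.

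Precision is also at stake. The trial plans 52 participants, and the article does not fix the use of the baseline score that would give the most power.

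**Working it through.** **Inputs.** From the article: difference 1.2 points, 26 per group, 80% power, significance level 0.05. Assumed: two-sided test, 1:1 allocation, complete data, equal SD at each visit, and baseline-to-later correlation r of 0.3, 0.5 or 0.7. Section 2.8.1 describes the tampon test's retest reliability only in words, so r is a range and not an estimate.

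**1. The plan's own figure.** Without an SD, the 26 per group can be neither reproduced nor refuted. Solving for the SD that gives 80% power (normal approximation):

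SD = 1.2 × √(26/2) / (1.960 + 0.842) = 4.327 / 2.802 = 1.54

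If only 21 per group are analysed (26 less 20%), the implied SD is 1.39. The first is used below; the second gives the same pattern (65.7/79.9/95.1% for change, 83.5/89.8/97.5% with baseline adjustment).

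**2. How often chance alters the model.** For k independent tests at 5%, the chance of at least one significant result is 1 − 0.95^k:

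| k | chance |
|---|---|
| 10 | 40% |
| 15 | 54% |
| 20 | 64% |

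Any one variable, such as a given baseline pain score, is flagged in about 5% of trials.

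**3. Power by use of baseline.** Power = Φ(1.2 / (SD_eff × √(2/26)) − 1.960), where SD_eff is:

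- later score alone: 1.54
- change from baseline: 1.54 × √(2(1 − r)). With complete data this is the group-by-time contrast of the mixed model with free baseline means.
- baseline-adjusted: 1.54 × √(1 − r²)

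| r | SD_eff, change | SD_eff, adjusted | Power, later score alone | Power, change | Power, adjusted |
|---|---|---|---|---|---|
| 0.3 | 1.82 | 1.47 | 80.2% | 66.1% | 83.8% |
| 0.5 | 1.54 | 1.33 | 80.2% | 80.2% | 90.0% |
| 0.7 | 1.19 | 1.10 | 80.2% | 95.2% | 97.6% |

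The gain from adjustment over the change contrast is about 18, 10 and 2 points, and it shrinks as r rises. Over a later-score model without baseline it is about 4, 10 and 17 points, and it grows.

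**4. What test-then-adjust achieves.** The rule was simulated for the baseline score in a later-score linear model (10,000 runs, 26 per group, SD 1.54):

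| r | Power, test-then-adjust | Power, always adjusted | Type I error, test-then-adjust |
|---|---|---|---|
| 0.3 | 78.8% | 81.5% | 5.0% |
| 0.5 | 79.6% | 88.3% | 4.6% |
| 0.7 | 80.4% | 96.9% | 3.5% |

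The rule recovers little of the available precision. The false-positive rate is not inflated; it becomes conservative as r rises.

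**The case against.** The strongest reply is that baseline pain is not left out. It is in the mixed model for everyone, with unstructured covariance. If the effect is the group-by-time contrast, a baseline pain difference is subtracted whether or not it is significant. This stands. A reader might infer from the rule that baseline pain is handled only by accident, or that a non-significant imbalance goes uncorrected in the mixed model. The article does not support that reading.

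The reply also holds on cause. The power loss in the mixed model comes mainly from free baseline means, and deleting the sentence alone would not recover it. With complete data, a covariate entered only as a main effect leaves the group-by-time contrast unchanged. The rule matters for that contrast when data are missing or when the covariate is allowed to act differently over time, and the article does not say which form is meant.

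Four further inferences are not supported:

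- **Inflated type I error.** The simulation shows none.
- **General linear models that definitely omit baseline.** The article names no baseline term, but it is a condensed account and the full plan is not shown. The later-score comparison applies only if they are run that way.
- **Recruitment source as a required covariate.** Participants come from clinic waiting lists "and through advertisements in social media", but nothing in the article shows that source predicts pain. Adding it would be a preference.
- **A need to replace the Mann-Whitney test on the 0–3 item.** That test is valid under randomisation, so a change would also be a preference.

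What survives is the rule itself. The article states it outright, so it is not a detail left to an unseen plan.

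**Conclusion.** The point holds in limited form. The rule chooses covariates by chance, leaves the model undetermined until the data are seen, and is incoherent if it selects baseline pain.

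Separately, the mixed model as described uses baseline less efficiently than it could: about 66/80/95% power against 84/90/98% with baseline adjustment, at r of 0.3/0.5/0.7. General linear models on later scores without baseline would have 80% against the same figures.

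These sizes rest on an SD of about 1.5 back-solved from the stated power, an assumed correlation, complete data, and the effect being read as change from baseline, which the article does not say explicitly. The 40% figure needs 10 independent tests. That count is illustrative, and correlation among the scales would lower it. The defect should be corrected, but it does not invalidate the trial.

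**What to change.** In section 2.9, delete the sentence on adjusting for variables that differ significantly at baseline, and state the adjustment in advance:

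- **Mixed model:** either use T0 as a covariate with T1 and T2 as the responses, or keep T0 as a response and constrain the two groups to a common baseline mean. Choose one and say so.
- **General linear models at T1 and T2:** include the baseline value of the outcome being analysed as a covariate.

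The cost is wording only. Section 2.8.2 states that the outcome measures are collected at T0, so no new data or participants are needed.

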#### Secondary outcomes

2.8.2

Secondary outcomes include pain acceptance, depression, anxiety, sexual function, and quality of life. To better our primary outcome measures, two other variables will also be analysed: unwillingness to perform the tampon test and abstinence from vaginal intercourse, both measured as binary variables.

Chronic pain acceptance questionnaire (CPAQ) is a self-assessment form used for patients with chronic pain and measures pain acceptance (Feliu-Soler et al., 2018; McCracken et al., 2004; Reneman et al., 2010). CPAQ is divided into two subscales: activity engagement (participation in activities despite living with pain) and pain willingness (attempts to avoid and control pain as pain management (ineffective coping) (Feliu-Soler et al., 2018; McCracken et al., 2004; Wicksell et al., 2009). The form consists of 20 statements that can be rated between “never true” to “always true”. CPAQ has good internal consistency and similar psychometric properties both when administered online or via paper-and-pencil (Fish et al., 2010; Wicksell et al., 2009).

The Female Sexual Function Index (FSFI) is an instrument for measuring female sexual function and consists of 19 questions within 6 domains: sexual desire, arousal, lubrication, orgasm, satisfaction, and pain (Rosen et al., 2000; Wiegel et al., 2005). Questions are rated on a Likert scale from 0 or 1 to 5, where 0 corresponds to no attempt at intercourse. Higher FSFI scores indicate better sexual functioning (Ter Kuile et al., 2006). Test-retest reliability has appropriate level of stability, while the internal consistency of the instrument and its subscales are satisfactory to good (Ter Kuile et al., 2006). The ability of the scale to predict the presence or absence of sexual complaints is considered excellent (Ter Kuile et al., 2006).

The Female Sexual Distress Scale-Revised (FSDS-R) is an instrument for measuring female sexual distress and consists of 13 questions (Derogatis et al., 2008). The score varies between 0 and 48 and each question can be rated from 0 (never) to 4 (always) (Derogatis et al., 2008). Higher FSDS-R scores indicate more sexual distress (Ter Kuile et al., 2006). The instrument has excellent reliability and good discriminant validity (Derogatis et al., 2008; Ghassami et al., 2014).

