Difficulties in recruiting are common in clinical trials and many trials may take longer to complete recruitment than primarily planned (Sully et al., 2013). Nevertheless, loss to follow-up seems to be a problem among internet interventions trials (Mathieu et al., 2013) and high dropout rates and low retention rates are a known issue among iCBT trials (Webb et al., 2017). An additional limitation of our study is the time period needed to conclude the recruitment phase, which has been prolonged due to dropouts and difficulties with retaining participants. To manage the issue of missing data, a per protocol approach will be used as a complement to ITT to facilitate interpretation of the findings (Beckett et al., 2016). Whilst ITT analysis has the advantage to preserve the balance afforded by randomisation, minimising the risk of for type I error and resembling clinical practice (Beckett et al., 2016; McCoy, 2017), a per-protocol approach may provide the true efficacy of an intervention among completers. LOCF is a common imputation method, but it has previously been criticized for overestimation of values as the true mean differences are not present when dropout rates differ between groups (Gueorguieva and Krystal, 2004; Lachin, 2016). Therefore, worst case imputation will be used to avoid inaccurate estimates and ensure the trustworthiness of the results.

Further, the specific limitations and practical problems encountered in this study may be of use for clinicians planning to implement this material. These should be taken into consideration when adjusting the content for use in clinical settings. A study involving qualitative analysis would be of value to further explore this issue and is now under way, which may have an impact on the planning of future studies.

At this point, there is a considerable knowledge gap when it comes to internet-based treatment for patients with vulvodynia. If effective, internet-delivered psychological treatment can easily be adapted and used in clinical settings to complement clinical treatment in a primary care setting.

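### Two unranked intention-to-treat analyses: LOCF and worst-case imputation are added beside the mixed model with heavy drop-out, and worst case is wrongly offered as the cure for inaccuracy

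*Protocol article*

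**What the plan says.** Section 2.9 (Statistical analysis plan) begins with linear mixed models for vulvar pain and other outcomes, including "quality of life over time, by applying the intention-to-treat approach". The stated reason for choosing them is: "Linear mixed modelling is a frequently recommended method for its abilities to handle missing data and correlated observations in repeated-measures data". No imputation is attached to this model.

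Because drop-out is expected, the same section adds general linear models at post-treatment (T1) and follow-up (T2), run under both ITT and per-protocol approaches. For these, "Last observation carried forward (LOCF) will be used for the intention-to-treat analysis". It continues: "Complementary analysis using worst case imputation and analysis using a per-protocol approach without imputation will also be carried out". One significance rule, p below 0.05, covers everything, and no ITT analysis is ranked above another.

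Section 5 (Discussion) concedes that "LOCF is a common imputation method, but it has previously been criticized for overestimation of values", and ties the problem to drop-out that differs between groups. It then draws the consequence that "worst case imputation will be used to avoid inaccurate estimates and ensure the trustworthiness of the results".

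Section 2.6 (Collection of data) reports, for the first 15 participants, 33% lost between baseline and T1, and 47% of those taking part at T1 lost by T2. It gives no split by arm.

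**The concern.** Two analyses of the same outcome at the same time points both carry the ITT label, and they handle missing women in incompatible ways. The mixed model uses only what was observed. The LOCF analysis assigns a woman lost before T1 her baseline pain, which amounts to assuming that she did not change. With a third or more of the data missing, the two can disagree, and the article does not say which one answers the trial's question.

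The stated remedy does not help. Giving each missing woman a bad score is a deliberately pessimistic assumption, not a more accurate one. If the same extreme score is used in both arms, the comparison becomes in part a comparison of drop-out rates. Drop-out could well differ here, because only one arm is asked to complete six modules at about 30 minutes a day (section 2.5), but the article reports nothing on this.

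**Working it through.** **Inputs from the article.** Pain scale 0 to 10 (section 2.8.1). Target difference 1.2 and 26 women per group (section 2.7). Loss rates as above (section 2.6).

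**Assumptions, not in the article.** Baseline mean 7.0. T1 means without loss of 6.0 (control) and 4.8 (intervention), so the true difference is 1.2 in favour of the intervention. Drop-out at random within arm. LOCF carries the baseline value. Worst case = 10 for every missing woman in both arms.

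**The plan's own figure.** The article states no standard deviation, so 26 per group cannot be reproduced. Solving 26 = 2(1.96 + 0.84)²SD²/1.2² gives SD about 1.54. If the 26 already allows for 20% loss, SD is about 1.38. The simulations below use SD 1.5 or 1.54 and a baseline-outcome correlation of 0.5.

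**Missing at T2.** As worded, 1 - 0.67 × 0.53 = 0.645. However, 47% is not a possible fraction of the 10 women left at T1. If 7 of 15 was meant, 47% are missing.

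**Expected difference (control minus intervention).** With m the proportion missing and V the imputed value, each arm's mean is (1 - m) × observed mean + m × V.

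- Equal 33% loss, LOCF: (0.67 × 6.0 + 0.33 × 7) - (0.67 × 4.8 + 0.33 × 7) = 6.33 - 5.53 = 0.80.
- Equal 33% loss, worst case: (0.67 × 6.0 + 0.33 × 10) - (0.67 × 4.8 + 0.33 × 10) = 7.32 - 6.52 = 0.80.
- Loss 45% intervention, 20% control, LOCF: (0.80 × 6.0 + 0.20 × 7) - (0.55 × 4.8 + 0.45 × 7) = 6.20 - 5.79 = 0.41.
- Same loss, worst case: (0.80 × 6.0 + 0.20 × 10) - (0.55 × 4.8 + 0.45 × 10) = 6.80 - 7.14 = -0.34.

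With equal loss, the general result is (1 - m) × 1.2. At T2 this gives 0.64 (47% missing) or 0.43 (64.5%) for worst case. It gives the same for LOCF only if baseline is the value carried; a woman seen at T1 would carry her T1 score instead.

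**When the sign reverses, with 20% loss in controls.**

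- Worst case, controls improving by 1: (1 - m) × (10 - 4.8) < 0.80 × (10 - 6.0), so intervention loss above 38.5%.
- Worst case, stable controls (means 7.0 and 5.8): (1 - m) × 4.2 < 0.80 × 3.0, so above 43%.
- LOCF, controls improving by 1: (1 - m) × 2.2 < 0.80 × 1.0, so above 64%.
- LOCF, controls improving by 2: (1 - m) × 3.2 < 0.80 × 2.0, so above 50%.
- LOCF, stable controls: never in expectation.

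**Rejection at the 5% level with no true effect (simulation, 26 per arm).** A dash means the figure is not available for that setting.

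| Loss, intervention / control | Improvement in both arms | Test | LOCF | Worst case | Observed data only |
|---|---|---|---|---|---|
| 33% / 33% | every trend tried | t-test | about 5% | about 5% | – |
| 40% / 27% | range over trends tried | t-test | 5–8% | 13–14% | – |
| 45% / 20% | 0 | t-test | 5% | – | – |
| 45% / 21% | 0 | ANCOVA | 4% | 31% | 5% |
| 45% / 20% | 1 | t-test | 9% | – | – |
| 45% / 21% | 1 | ANCOVA | 10% | 35% | 5% |
| 45% / 20% | 2 | t-test | 18% | 40% | – |
| 45% / 20% | 2 | ANCOVA | 24% | 41% | 5% |

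The worst-case rejections mostly point against the intervention: at 45% / 21% with a 1-point improvement, the mean estimate is 0.96 points more pain in that arm when the truth is zero.

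**Power for a true 1.2 with equal 33% loss** (ANCOVA, controls improving by 1, SD 1.5): 0.74 on observed data, 0.53 with LOCF, 0.22 with worst case.

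**The case against.** The strongest reply is that the sound analysis is already in the plan and comes first. The mixed model is ITT, needs no imputation, and the imputed analyses are introduced afterwards as additional or complementary. This stands. A reader might infer that the trial's ITT conclusions rest on LOCF and worst-case imputation; section 2.9 does not support that. What remains is that LOCF is fixed as the ITT rule for a second set of models, with nothing to subordinate it.

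A reader might also infer that both imputations can readily reverse the effect. With equal loss they only dilute it, and false rejection stays near 5%. Reversal needs unequal loss, which the article does not report; its rates come from 15 women. A moderate imbalance is enough for worst case. LOCF keeps the right sign in the 45% / 20% example and reverses only with a more extreme imbalance and improving controls. Likewise, the 18% false rejection for LOCF needs both the imbalance and a 2-point improvement in both arms; without a time trend it is about 5%.

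The worst-case value is not defined, so the score of 10 in both arms is an assumption. A condensed article may leave that definition, and perhaps a ranking of analyses, to a fuller plan, and a missing definition is not criticised here. The Discussion's justification is different: it is stated, and it is wrong.

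Finally, the observed-data results assume drop-out at random within arm, which suits the mixed model. That is a reason for a sensitivity analysis, but not for these two imputations.

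**Conclusion.** The point holds in this limited form and should be fixed. The article sets an LOCF analysis labelled ITT, with a worst-case version, beside an ITT mixed model without saying which decides. It keeps LOCF after conceding its weakness, and it credits worst-case imputation with an accuracy that it does not have.

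The part that needs no assumption about unequal drop-out is the dilution: at 33% loss in both arms, a true 1.2, which section 2.7 treats as the minimum clinically significant improvement, is expected to appear as about 0.80 under either imputation. The larger distortions (0.41 for LOCF, -0.34 for worst case, and false rejection of roughly 30–40% for worst case against 5–18% for LOCF by t-test) depend on the assumed 45% / 20–21% imbalance, the assumed means and time trends, and 10 as the imputed score. They show what the rules could do, not what the trial's data will do.

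Section 2.8.2 also gives the FSDS-R 13 items scored 0 to 4 but a maximum of 48, whereas 13 × 4 = 52. A reader might infer that 48 would be used as an imputed worst score. Nothing in the article says so; this is a separate minor slip and adds no weight here.

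**What to change.** 1. In section 2.9, name the linear mixed model, with all randomised women and no imputation, as the single primary ITT analysis.
2. Drop LOCF, or keep it only as a labelled sensitivity analysis that cannot override the mixed model. Either settles the conflict.
3. Replace worst-case imputation with multiple imputation and a delta-adjusted (tipping-point) analysis: worsen the imputed pain scores in stated steps, separately by arm, and report the shift at which the conclusion changes.
4. In section 5, withdraw the statement that worst-case imputation avoids inaccurate estimates.
5. Separately, correct the FSDS-R range in section 2.8.2 to 0–52, to agree with 13 items scored 0 to 4.

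The cost is some additional analysis work and no new data. These changes remove the bias that the imputation rules introduce; they do not restore information. With 33% missing, power for 1.2 points is about 0.63 to 0.73 (normal approximation, SD 1.54 to 1.38), and lower at T2.

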**Methods:**

We will randomise 52 patients to either guided internet-based intervention with CBT with (ACT) components or no intervention during the waiting period for treatment as usual. Online assessments are conducted at baseline, posttreatment, and at follow-up after 9 months. The primary outcome measure is provoked vulvar pain. Secondary outcomes are depression, anxiety, sexual function, and quality of life. Linear-mixed effect models will be used to assess the effect of the internet-based intervention on vulvar pain, pain acceptance, depression, anxiety, sexual function, and quality of life over time, by applying the intention-to-treat approach. Continuous data will be analysed with general linear models using intention-to-treat and also per protocol approaches to assess the effects of the intervention at different time points. Ordinal and binary data will be analysed with Mann Whitney's test, Fischer's exact test and multivariate logistic regression, respectively.

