### Collection of data

2.6

Online assessments are conducted at baseline (T0), posttreatment (6 weeks after randomisation, T1), and at follow-up (9 months after randomisation, T2). Self-reported online questionnaires generally have the same psychometric properties as paper-and-pencil administrated questionnaires (Buchanan, 2003). Three emails are sent as reminders for each assessment. A flowchart of the study is presented in Fig. 3. Among the first 15 participants, the drop-out rate between baseline and post-treatment is 33%, while 47% of those participating in post-treatment are lost to follow-up.

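### With about 18 to 35 women analysed, an ordinary multivariable logistic model for the two binary outcomes is unreliable and Fisher's test gives up some power; Firth's fit and Boschloo's test are a cheap improvement

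*Protocol article*

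**What the plan says.** Section 2.9 gives the Mann-Whitney test to the ordinal outcome. It gives the two binary outcomes Fisher's "exact test and multivariate logistic regression, respectively, to assess differences between groups at posttreatment and follow-up". These are labelled secondary, are restricted to the per-protocol set, and are to be run in SPSS. On significance, 2.9 states that P "values less than 0.05 will be considered statistically significant". It gives no estimator and no covariate list for the logistic model.

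Section 2.8.2 introduces the variables as "unwillingness to perform the tampon test and abstinence from vaginal intercourse, both measured as binary variables", added to strengthen the primary pain measures. It also says that all measures except the relationship scale are collected at T0, T1 and T2, so baseline values of both binary variables exist.

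For the numbers, the Abstract says "We will randomise 52 patients to either guided internet-based intervention". Section 2.4 uses simple randomisation. Section 2.6 reports, for the first 15 participants, that "the drop-out rate between baseline and post-treatment is 33" percent, with 47% then lost by follow-up. Section 2.7 plans for 20% drop-out.

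**The concern.** Both named methods are sensitive to small numbers. A logistic model fitted by maximum likelihood with few events per coefficient gives odds ratios too far from 1. It can also separate: a combination of covariates predicts the outcome perfectly and the odds ratio is infinite. Fisher's test conditions on both margins, so few p-values are attainable and its true error rate lies below 5%, which costs power.

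The outcomes are secondary but useful. A woman who does not attempt the tampon test or intercourse has no provoked-pain score for it, so these variables help a reader interpret the pain result. An inflated or infinite adjusted odds ratio would mislead there, and lost power would hide a real change.

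**Working it through.** **1. The plan's own figure.** The article gives no sample size, power or event rate for the binary outcomes. Section 2.7 says "A minimum of 26 patients in each group at each time point is estimated to give 80% power", but for a 1.2-unit pain difference. No SD is stated, so that figure cannot be reproduced. It would need an SD near 1.54 without a drop-out allowance: 2 × (1.96 + 0.84)² × 1.54² / 1.2² ≈ 26. It does not bear on the binary outcomes.

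**2. Women analysed.**
- T1: 52 × (1 − 0.33) ≈ 35.
- T2, if 47% is of those seen at T1 (as written): 52 × 0.67 × 0.53 ≈ 18.
- T2, if 47% is of all 15 (7/15 = 47%, whereas 47% of 10 is not a whole number): 52 × 0.53 ≈ 28.
- At the planned 20% drop-out: 52 × 0.80 ≈ 42.

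Per-protocol exclusions can only lower these.

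**3. Logistic regression, by simulation.** Odds ratios, event rates and covariate counts are all assumptions.

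*True odds ratio 0.4, control rate 25% to 40%, three to five modest covariates (2,500 runs per setting):*

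| Women | Inflation of mean log odds ratio | Fits that fail |
|---|---|---|
| 35 | 17% to 40% | 1% to 14% |
| 28 | 11% to 53% | 4% to 28% |
| 18 | not summarised | 20% to 66% |

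With three covariates the inflation is about 20% to 30%. Firth's fit stays within about 6% of the truth at 28 to 35 women and gives finite estimates.

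*True odds ratio 3 (log 1.10), control rate about 30% (600 runs per setting). This is milder because events are less sparse, with about 7 women in the rarer class at N = 18 and 15 at N = 35:*

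| Women | Added covariates | Mean log odds ratio, ML | Inflation | Separation | Mean, Firth |
|---|---|---|---|---|---|
| 35 | 1 | 1.26 | 15% | 0.3% | 1.14 |
| 35 | 3 | 1.37 | 25% | 0.3% | 1.14 |
| 35 | 5 | 1.51 | 37% | 0.3% | 1.12 |
| 18 | 1 | 1.50 | 36% | 4% | 1.15 |
| 18 | 3 | 1.98 | 80% | 10% | 1.16 |
| 18 | 5 | 2.27 | 106% | 30% | 1.15 |

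Inflation is the ML mean divided by 1.10, minus 1. The ML means use only runs with a finite estimate, and at 18 women a few near-separated runs pull them up. The median odds ratio with three covariates is 4.32 at 18 women and 3.79 at 35, against a true 3. At 28 women Firth's mean lies between 1.07 and 1.20, so within about 9% of 1.10.

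**4. Fisher against Boschloo, by exact enumeration.** For arms n1 and n2 and a common rate p, size(p) = Σ Bin(a; n1, p) × Bin(b; n2, p) over all tables with two-sided Fisher p < 0.05. Maximum size is the largest value over p. Boschloo's test uses the Fisher p as its ordering statistic and resets the cut-off so that the maximum stays at or below 5%. Its rejection region contains Fisher's, so it is never less powerful.

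| Split | Fisher maximum size | Rates compared | Power, Fisher v Boschloo |
|---|---|---|---|
| 9/9 | 2.1% | 20% v 60% | 28% v 35% |
| 13/13 | 2.9% | 40% v 10% | 28% v 43% |
| 14/13 | 3.3% | 40% v 10% | 34% v 34%, or 40% v 41% |
| 17/17 | 2.4% | 50% v 15% | 46% v 57% |
| 18/17 | 4.1% | 50% v 15% | 53% v 57%, or 57% v 61% |
| 26/26 | 2.8% | 50% v 15% | 71% v 79% |
| 28/24 | 4.0% | 50% v 15% | 74% v 76%, or 77% v 77% |

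Two entries mean that the result depends on which arm is larger.

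Averaged over simple 1:1 randomisation, with event rates from 10% to 50% for size:

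| Women | Fisher's average size | Power, 50% v 15% | Power, 40% v 10% |
|---|---|---|---|
| 18 | 0.5% to 2.7% | 24% v 30% | 18% v 24% |
| 28 | 0.8% to 2.8% | 41% v 48% | 34% v 42% |
| 35 | 1.5% to 3.9% | 53% v 59% | 46% v 53% |

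With 20% v 60% included, the averaged gain is 3 to 8 points.

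**The case against.** **Fisher's test is valid.** It controls the type I error, and the article states nothing false in choosing it. This stands: the Fisher part concerns efficiency only.

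**The conservatism is easily overstated.** A reader who enumerates only equal arms might infer that the real error rate here is about 2% and never above 2.9%. The document does not support that. Section 2.4 uses simple randomisation, drop-out follows, and 35 women cannot split equally; 18/17, 19/16 and 20/15 all give a maximum of 4.0% to 4.1%. The 15-point gain at 13/13 shrinks to 0 or 1 point at 14/13. Unequal splits do not always remove it, since 20/15 reaches 15 points in one setting.

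**The logistic details are not in the article.** Maximum likelihood is inferred from an unqualified logistic regression in SPSS. The number of covariates is unknown, and a condensed article may leave it to a fuller plan, so its absence is no fault. A reader might infer that the odds ratios will generally be inestimable. That does not follow: with one covariate at 35 women and a true odds ratio of 3, separation is 0.3% and inflation 15%. What remains is that the article commits to a multivariable model at a size where each added covariate makes matters worse.

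**The numbers may improve.** The retention rests on 15 women. At 42 women and a true odds ratio of 3, three covariates give a mean log odds ratio of 1.27 (15% inflation) and no separation was seen.

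**Conclusion.** The point holds as a cheap improvement to two secondary analyses. The logistic part is the stronger. At about 18 to 35 women, an unpenalised model with three covariates inflates the log odds ratio by roughly 20% to 30% at a true odds ratio of 0.4. Separation ranges from a few percent of trials at 35 women to roughly a quarter or more at 18, and is lower (0.3% and 10%) in the milder odds-ratio-3 setting. These sizes rest on assumed event rates and covariate counts, an inferred estimator, and retention seen in 15 women.

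For Fisher's test, maximum size is about 2% to 4% by number and split. Boschloo's gain is 0 to 15 points by split, typically 3 to 8 on average. Most of the low power at T2 is due to the number of women: at 18, neither test exceeds 30% for 50% v 15%. A reader might infer that the trial's main result is at risk; it is not, because these variables are secondary and the pain analysis does not use these methods.

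**What to change.** In section 2.9:
- Limit the logistic model for each binary outcome to group plus the T0 value of the same variable, fitted with Firth's penalised likelihood. The T0 value may itself predict the later answer almost perfectly, which is a further reason for the penalty.
- Use Boschloo's exact test in place of Fisher's, and report the risk difference with a Newcombe or Miettinen-Nurminen 95% confidence interval.

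This takes about two sentences and needs no new data or participants. The small downside is that both methods need R or an SPSS extension, so the statement that all analyses use SPSS needs a matching change.
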